## Abstract

**Background:**

Cognitive problems are common in non-central nervous system cancer survivors. These problems are perceived as an important contributor to decline in work performance and work ability. Various interventions for cognitive problems have been proposed, but effectiveness regarding work-related outcomes has not yet been established. Effective treatment options to alleviate the adverse influence of cognitive problems on work performance are needed for working cancer survivors. In this paper, we will describe the design of a randomized, controlled, multicenter trial that evaluates the (cost-)effectiveness of an Internet-based cognitive rehabilitation program for occupationally active cancer survivors confronted with cognitive problems.

**Methods/ design:**

A three-armed randomized controlled trial will be conducted, including two intervention groups (i.e., basic and extensive cognitive rehabilitation program) and one waitlist control group. In total, 261 cancer survivors (18–65 years) who have returned to work and who experience cognitive problems will be recruited. Patients with and without cognitive impairment as established in a neuropsychological assessment will be eligible; stratification will take place based on the presence of this cognitive impairment. The extensive intervention arm will contain a comprehensive training program (including psycho-education, fatigue management, and cognitive strategy training) with individual guidance (blended intervention). The basic intervention arm will contain a brief cognitive training program (including psycho-education and fatigue management) without individual guidance. The primary outcome will be accomplishment of an individually defined work-related treatment goal. Secondary outcomes include, among others, subjective cognitive functioning, work functioning, and quality of life. Primary and secondary outcomes will be measured at baseline (T0) and at 12 weeks (T1) and 26 weeks (T2) post-randomization.

**Discussion:**

About 40–50% of the cancer patients worldwide are of working age at time of diagnosis. Many of the occupationally active cancer survivors experience cognitive problems. Both from an individual and a societal perspective, it is important to sustain cancer survivors’ employability. An effective treatment to alleviate the impact of cognitive decline and to improve work ability might help cancer survivors to sustain employability.

**Trial registration:**

ClinicalTrials.gov NCT03900806. Registered on 03 April 2019 (current status: ongoing).

## Background

Non-central nervous system (CNS) cancer and its treatment can be associated with cognitive problems [1–4]. Up to 78% of non-CNS cancer patients have reported to experience cognitive problems in the active treatment period. While previous studies have shown that cognitive problems improve after completion of therapy [5, 6], a substantial subgroup (approximately 30–40%) of patients is confronted with cognitive problems that can last for months or even up to 10 years post-therapy [1, 5–8]. Although cognitive problems in non-CNS cancer patients are generally mild, even subtle changes in cognitive function can have a significant impact on a patient’s quality of life [9].

About 50% of the 3.45 million people diagnosed with cancer each year in Europe is part of the working population [10], of whom 89% manage to return to work (RTW) within 24 months [11]. Cancer patients rate employment as the third most important aspect of their quality of life [12]. Being able to work is a sign of recovery, and it contributes to patients’ self-esteem. Still, cancer survivors report effects of cognitive problems, such as problems related to memory, concentration, attention, and executive functioning, as highly affecting their work performance [11, 13–15]. Avoidable work disability and consequent productivity losses should be reduced. From both a patient and a societal perspective, it is therefore of relevance to provide evidence-based treatment options for working non-CNS cancer survivors confronted with persistent cognitive problems.

Whereas numerous studies have been performed evaluating the effectiveness of interventions to support cancer patients in their RTW process [16], there is a lack of interventions to accomplish sustainable employability [17]. From the literature so far, cognitive impairment seems to be only weakly associated with RTW [13], but its impact on work-related problems at the workplace appears to be substantial [10]. This underlines the need for effective vocational cognitive rehabilitation, implemented in a phase that patients already have achieved RTW.

So far, evidence-based treatment options for cancer survivors experiencing cognitive problems are limited [18, 19]. In other neurological patient populations, meta-cognitive strategy training has shown to be successful in improving daily life functioning, using intact cognitive abilities and strategies together with psycho-education. By teaching patients compensatory strategies to achieve the same behavior in a different way, intact neural circuits might be reorganized and different neuropsychological systems might be used [20]. Meta-cognitive strategy training appears to be a promising treatment for cancer patients as well. That is, there is evidence regarding improvement in areas of daily life functioning, in self-perceived cognitive function, and to a lesser extent, in tested cognitive function [6, 18, 21–24]. However, since results are neither robust nor consistent, additional studies are required to establish effectiveness of meta-cognitive strategy training for non-CNS cancer survivors.

Internet-based interventions are gaining ground in the field of cognitive rehabilitation [25–30] as they empower self-management regarding patients’ own health care. Cancer survivors perceive flexibility in use (i.e., accessible where and when the patient likes) as an important component to the development of any treatment for cognitive changes [31]. Furthermore, Internet-based delivery may be more economical than face-to-face therapy as it requires less therapist time. In addition, the overall mean effect size of Internet-based psychotherapeutic interventions is comparable to the effect size of traditional face-to-face interventions, indicating that these interventions are an effective treatment method [32].

In the current study, we will develop both a basic and an extensive version of an Internet-based cognitive rehabilitation program for occupationally active cancer survivors with persistent cognitive problems. The intervention consists of different elements from meta-cognitive strategy training that have been shown to be effective in managing symptoms, such as problems related to memory, concentration, attention and executive functioning, and fatigue. In this article, we describe the design of a randomized, controlled, multicenter trial in which the (cost-)effectiveness of this Internet-based cognitive rehabilitation program on work-related outcomes will be evaluated. It is hypothesized that both cancer survivors who undergo the basic or extensive cognitive rehabilitation program will achieve more often their pre-set work-related rehabilitation goals, compared to cancer survivors in the waitlist control group. Furthermore, it is hypothesized that cancer survivors with cognitive impairment at study entry (as measured with neuropsychological tests) will be better at achieving their pre-set rehabilitation goals when allocated to the extensive cognitive rehabilitation program compared to the basic cognitive rehabilitation program. Finally, we hypothesize that both the basic and extensive cognitive rehabilitation program will be cost-effective compared to the control group. If found to be (cost-)effective, this Internet-based cognitive rehabilitation program can be embedded as standard practice in the growing community of occupationally active cancer survivors experiencing cognitive problems at work.

## Methods/design

### Study design

A multicenter, three-armed randomized controlled trial will be conducted to evaluate the effectiveness of an online cognitive rehabilitation program. Two intervention groups (i.e., a basic and an extensive cognitive rehabilitation program) and one waitlist control group will be included. An economic evaluation will be conducted to assess cost-effectiveness of the cognitive rehabilitation program. Furthermore, a process evaluation will be performed to evaluate the procedures regarding recruitment, execution and implementation of the cognitive rehabilitation program. This study will be conducted by the Netherlands Cancer Institute, Amsterdam, the Netherlands. Participants will be cancer survivors who are treated for cancer in several (university) hospitals in the Netherlands. The study has been approved by the Medical Ethic Committee at the Netherlands Cancer Institute and is registered at ClinicalTrials.gov (registration number NCT03900806).

### Study sample

The study sample will be composed of 261 men and women of working age (18–65 years) with histologically confirmed non-CNS cancer. Eligible participants should have been treated with chemotherapy, targeted agents, and/or immunotherapy, which should have been completed a minimum of 6 months before study entry. Patients who are still receiving hormonal therapy can be included in the trial. Since it is expected that cognitive problems affect work in the first period after RTW most prominently, cancer diagnosis can be at the utmost 42 months ago at study entry. Eligible patients should self-report cancer and/or cancer treatment-related cognitive problems. This will be assessed by the study team during a screening. Both patients with and without cognitive impairment according to neuropsychological tests (i.e., a *z*-score of 1 under or above the mean score of a control group, on at least two tests of the different cognitive domains compared to the normative data of a healthy population by age) will be included in the study. Furthermore, eligible participants should be occupationally active for a minimum of 12 working hours per week and have a fixed or temporary employment contract (with at least 6 months left of their contract).

Patients will be excluded from the trial if they lack basic proficiency in Dutch, have a serious overt psychiatric or neurological disorder that can interfere with the study aims, or have no Internet access. In addition, patients will be excluded if they participate in comparable studies or programs focused on the reduction of cognitive problems and/or on the support of patients to retain work.

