### Recruitment and randomization

Cancer patients will be identified through the Netherlands Cancer Registry and recruited via treating physicians of several (university) hospitals in the Netherlands. Potentially eligible patients will receive a personalized letter from their treating physician, informing them about the study and the cognitive rehabilitation program. Patients will be asked to respond via post (response card), email, or phone whether or not they are interested in participation. In case a patient does not respond, a reminding letter will be sent after 3 weeks. Patients who express interest in participation will receive a phone call from the study team for further screening (e.g., a check of their employment status) and to provide additional information about the trial. Patients will be invited by e-mail to complete the baseline measurement (i.e., an online questionnaire and an online neuropsychological assessment) in case they fulfill all criteria, are motivated, and are willing to comply to the trial procedures. After completion of this baseline measurement, a session (face-to-face or using videoconference) with a therapist (e.g., neuropsychologist, occupational therapist) will be planned to discuss outcomes of the neuropsychological assessment, followed by collaborative treatment goal setting.

Upon receipt of all baseline information and after the session with the therapist, patients will be randomly allocated to the basic intervention arm (*N* = 87), the extensive intervention arm (*N* = 87), or the waitlist control group (*N* = 87), using randomized design in the computerized program ALEA. Minimization will be applied for the presence of cognitive impairment on the neuropsychological assessment to equalize group sizes. Blinding of participants and professionals is not possible for this type of intervention. Further, blinding for assessment is not applicable since measurements will be computer-based. A flow diagram of the recruitment procedure is outlined in Fig. 1. Figure 2 shows a schedule of enrolment, interventions, and assessments.

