**Fig. 3 Fig3:**
[figure not shown]
Dependent and independent measures, mediating and moderating processes

**Table 2 Tab2:** Study measures and corresponding instrument

Variable	Instrument	Details
*Primary outcome*		
Goal Attainment Scaling	GAS	▪ 3 personalized treatment goals
		▪ 6-point scale
*Secondary outcomes*		
Cognitive problems	CSC-W DV	▪ 19 items, 5-point scale
		▪ Score range: 0 (never) to 4 (always)
		▪ Cronbach’s alpha: 0.95
Work ability	WAI	▪ 1 item, 10-point Likert scale
Work functioning	WRFQ	▪ 27 items
		▪ Range 0 to 100; higher scores indicate better work functioning.
		▪ Subscales: work scheduling demands, mental demands, social demands, physical demands, and output demands
		▪ Cronbach’s alpha: 0.91–0.96
Absenteeism and presenteeism	iPCQ	▪ 6 items
		▪ Subscales: absenteeism, presenteeism
Need for recovery	VBBA	▪ 11 items (subscale)
Health-Related Quality of Life	SF-36	▪ 36 items, dichotomous and 3- to 6-point Likert scales
		▪ Subscales: vitality, physical functioning, bodily pain, general health perceptions, physical role functioning, mental health, emotional role functioning, and social role functioning
		▪ Score range: 0–100; higher score indicates higher levels of functioning/ well-being.
		▪ Time frame: past week
		▪ Cronbach’s alpha: 0.66–0.91 (mean 0.84)
Fatigue	SF-36	▪ 4 items (subscale)
Coping	CERQ	▪ 36 items, 5-point Likert scale
		▪ Score range: 0 (never) to 5 (always)
		▪ Subscales: self-blame, acceptance, rumination, positive refocusing, refocus of planning, positive reappraisal, putting in to perspective, catastrophizing and other blame
Neuropsychological function	ACS	▪ 7 different neuropsychological tasks
		▪ Online assessment
		▪ Cognitive domains: executive functioning, information processing speed, attention, working memory, verbal learning and memory, psychomotor speed.
		▪ The ASC is usable a reliable for the oncology setting, with test–retest correlations in the range 0.29 up to 0.78, which is comparable with traditional tests.
		▪ Concurrent validity with traditional tests is medium to large.
Work involvement	WIS	▪ 6 items, 5-point scale
		▪ Score range: 1 (totally disagree) to 5 (totally agree). High scores indicate a high work involvement
Job characteristics	JCQ	▪ 35 items, ordinal 4-point scales
		▪ Score range: 1 (totally disagree) to 4 (totally agree).
Depression and anxiety	HADS	▪ 14 items, 4-point Likert scale
		▪ Subscales: depression, anxiety
		▪ Score range: 0–42
		▪ Time frame: past week

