In this study, GAS will be used as the primary study endpoint, evaluating between-group differences over time in GAS scores. The GAS scores will be calculated according to published scoring algorithms (see the “Methods/design” section). To evaluate intra-individual differences in the trajectory of change over time for the primary outcome, we will use a growth curve modeling approach with random intercept and slope. This approach takes into account the within- and between-person variability and deals adequately with missing data [51]. Both linear and quadratic effect of time will be modeled to determine if an initial improvement or deterioration in the outcome was followed by a deceleration of this change over time. Appropriateness of the final model (with or without quadratic effect) will be determined based on model fit statistics: the Bayesian information criterion [52] and the Akaike information criterion [53]. In all analyses, the control group will be the reference group. Furthermore, moderation analysis will be conducted to determine whether the interventions have a differential effect among the subgroups classified as cognitive impaired yes or no (measured by ACS) at baseline. Baseline differences will be accounted for in the model. In case of non-ignorable dropout, we will correct the model for different patterns of missing values [54]. All analyses will be done on an intention-to-treat basis. Furthermore, as a secondary analysis, per-protocol analyses will be performed on patients who met criteria for minimal compliance (i.e., at least 4 logins into the online program) with the intervention(s). Differences in mean change scores over time between the intervention groups and the control group will be accompanied by effect sizes. Effect sizes of 0.2 are considered small, 0.5 moderate, and 0.8 large [55]. Effect sizes of approximately 0.5 are considered to be clinically relevant [56].

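### The stated impairment rule counts scores above the norm as well as below it, without saying that 'above' applies only where a higher score is worse; taken literally, it blurs the hypothesis 2 subgroup.

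*Protocol article*

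**What the plan says.** The Study sample section admits patients with and without impairment on testing. It gives the document's only working rule for telling them apart, a z-score threshold: "of 1 under or above the mean score of a control group, on at least two tests of the different cognitive domains". The yardstick for that threshold is healthy people of similar age. Table 2 describes the ACS battery as "7 different neuropsychological tasks" and lists six domains, among them processing speed and psychomotor speed.

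The resulting flag is used in three places:

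- **Allocation** (Recruitment and randomization): "Minimization will be applied for the presence of cognitive impairment on the neuropsychological assessment to equalize group sizes". No other allocation factor is named.
- **Hypothesis 2** (Background): "cancer survivors with cognitive impairment at study entry (as measured with neuropsychological tests) will be better at achieving their pre-set rehabilitation goals" when given the extensive rather than the basic programme.
- **Analysis** (Statistical analysis): moderation is tested across "subgroups classified as cognitive impaired yes or no", measured by the ACS at baseline.

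The Sample size calculation section justifies a fourfold inflation, to 261 patients, by the subgroup analysis for this second hypothesis.

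**The concern.** Impairment has a direction and the stated rule has none. A survivor who scores 1 SD better than age norms on two tests meets it as fully as one who scores 1 SD worse. So does someone with one good and one poor score. The text does not say that scores are first aligned so that lower is worse, nor that 'above' is reserved for times or error counts.

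If the rule were programmed as written, the impaired group would mix low scorers with people who have no deficit by the usual meaning. Any extra benefit of the extensive programme that is confined to true low scorers would be averaged with patients in whom it is absent, in the very subgroup for which the sample was enlarged. Minimisation would also balance the arms on the wrong characteristic.

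**Working it through.** The document gives no expected impairment rate, so there is no stated figure to reproduce. The calculation below only sizes the consequence of the wording.

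**Inputs from the document:** threshold of 1 SD, read as at least 1; at least two tests; seven tasks (Table 2); six domains (Table 2).

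**Assumptions not in the document:** normal z-scores with higher meaning better; equal inter-test correlation between 0 and 0.5; sample mean at the norm, 0.3 SD below it or 0.5 SD below it. Any two of the seven tests count, so the different-domains condition is ignored.

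**Exact case: independent tests, sample at the norm.** With p the chance that one test counts,

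P(at least 2 of 7) = 1 − (1 − p)^7 − 7p(1 − p)^6.

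- Poor scores only, p = P(z ≤ −1) = 0.1587: 1 − 0.2984 − 0.3939 = 0.308.
- Both directions, p = P(|z| ≥ 1) = 0.3173: 1 − 0.0691 − 0.2249 = 0.706.

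With six scores, one per domain, the same formula gives 24.4% and 61.6%.

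**Correlated tests** (simulation, at least 500,000 draws per row, seven tests). Everyone flagged by the one-sided rule is also flagged by the two-sided rule, so the share added by 'above' is 1 − (one-sided ÷ two-sided).

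| Mean shift | Correlation | As written | Poor scores only | Flagged only because 'above' counts (% of flagged) | Two or more high scores, no low score (% of flagged) |
|---|---|---|---|---|---|
| 0 | 0 | 70.6% | 30.8% | 56% | 17% |
| 0 | 0.2 | 68.8% | 30.4% | 56% | 29% |
| 0 | 0.4 | 63.9% | 28.8% | 55% | 38% |
| 0 | 0.5 | 60.2% | 27.8% | 54% | 42% |
| −0.5 SD | 0 | 80.7% | 68.9% | 15% | 1% |
| −0.5 SD | 0.2 | 76.2% | 60.6% | 20% | 6% |
| −0.5 SD | 0.4 | 70.4% | 54.5% | 23% | 12% |
| −0.5 SD | 0.5 | 66.6% | 51.7% | 22% | 15% |

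At a shift of −0.3 SD the shares are 63–75% as written and 42–54% one-sided, with 28–34% of those flagged added by 'above'.

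**Effect on hypothesis 2.** Suppose the extra benefit of the extensive programme is Δ in true low scorers and zero in everyone else. The flagged group then shows Δ × (one-sided ÷ two-sided), and the unflagged group shows zero. The contrast retained is:

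- sample at the norm: 30.8 ÷ 70.6 = 0.44 up to 27.8 ÷ 60.2 = 0.46;
- sample 0.5 SD below: 54.5 ÷ 70.4 = 0.77 up to 68.9 ÷ 80.7 = 0.85, a loss of 15–23%.

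**The case against.** The strongest reply is that nobody would call a high performer impaired, and that the phrase has an innocent meaning. Two are available.

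1. 'Above' may refer to time or error scores, where high is worse. The speed domains in Table 2 make this natural. The actual classification could then be correct, leaving only a fault of wording. This stands as a plausible intention, but the sentence does not say it.
2. The phrase may describe the two groups, impaired below and unimpaired above. As a yes/no rule this fails: patients with fewer than two low and fewer than two high scores would belong to neither group, which is 28–45% of the sample in the same scenarios.

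It is also fair that a condensed article need not list the scoring direction of each task. But the article chose to state the rule, and as stated it is wrong rather than merely brief.

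Three points on size stand. The 71% against 31% comparison describes norm-level people with independent tests, whereas participants must report cognitive problems. Patients added by 'above' include some with one genuinely low score, so not all are good performers: at −0.5 SD, those with two or more high scores and no low score are only about 1–10% of the whole sample. And enforcing different domains lowers the shares somewhat, as the six-score version shows.

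A reader might infer that the trial has in fact classed good performers as impaired, or that its allocation is compromised. The document supports neither. It does not show how the flag was programmed in ALEA. A poorly chosen baseline factor does not bias the comparison of arms, and hypothesis 1 does not use the flag to define its comparison.

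**Conclusion.** The definition is wrong as written and should be corrected. Whether any patient has been misclassified cannot be told from the document.

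If the rule is applied literally, and on the assumptions above, it flags 60–71% instead of 28–31% of a sample at the norm, and 67–81% instead of 52–69% of a sample 0.5 SD below it. In the second case 15–23% of those flagged would not meet a one-sided rule. The direction of the error is the same in every scenario tried; its size depends on the assumed shift and correlation, neither of which the document gives.

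The consequence is confined to a weaker hypothesis 2 contrast and poorer balance on true impairment.

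**What to change.** - State that impairment means a z-score of −1 or lower, after every test is aligned so that lower is worse, on at least two tests from different domains, against age norms.
- Check the scoring script against that sentence.
- Use this one flag for minimisation and for the moderation analysis.
- If ALEA has already used a different flag, derive the corrected flag for the hypothesis 2 analysis and also adjust for the flag used at allocation.

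The cost is one sentence and a script check; no new data are needed. Adding a moderation analysis on a continuous ACS score is optional and not part of this correction.
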